## Abstract

**Background:**

Knowledge about gaming disorder has increased in recent years. However, more research is needed regarding treatment options for gaming disorder. The most studied treatment option today is cognitive behavioral therapy (CBT). However, due to the low number of high-quality trials, the certainty in the evidence is low. Only a handful of previous studies are randomized controlled trials, further affecting the evidence level. Many previously studied treatments are also resource-intensive, making it difficult to implement in routine care. In addition, few treatment studies so far include adults. Therefore, we aim to evaluate a flexible manual-based CBT-program for gaming disorder in a randomized controlled trial, including both adults and adolescents.

**Methods:**

A total of 160 patients will be recruited. Participants will be randomized to an intervention group receiving CBT treatment for approximately 12 weeks or to a waitlist control group. The primary outcome measure is the score on the Internet Gaming Disorder Scale 9- Short form. The questionnaire measures severity of gaming disorder before and after treatment. Assessments will be made at five time points, from the first visit to a 3-month follow-up. The participants randomized to the control group will remain on a waitlist for 12 weeks. During this time, the participants in the control group will receive the same questionnaires at the same time points as the intervention group. After 12 weeks, the control group will be offered the same treatment as participants in the intervention group. In an additional study, all participants will be followed up until 24 months after treatment.

**Discussion:**

This trial will evaluate the effects of a 12-week CBT-treatment for patients with gaming disorder, compared to no treatment. Increasing the knowledge of the effectiveness of CBT for gaming disorder will improve the ability to offer evidence-based care for this group of patients.

**Trial registration:**

Clinicaltrials.gov NCT05328596. Registered on April 22, 2022.

## Administrative information

Note: the numbers in curly brackets in this protocol refer to SPIRIT checklist item numbers. The order of the items has been modified to group similar items (see http://www.equator-network.org/reporting-guidelines/spirit-2013-statement-defining-standard-protocol-items-for-clinical-trials/).

## Introduction

### Background and rationale {6a}

Gaming has become increasingly popular since it was introduced in the 1970´s. The rapid development of video games and online gaming, especially in the last decade, has made gaming a very popular activity in broader society. In a report from Europe’s Video Games Industries 2023, 53 percent of the population aged 6 to 64 reported gaming in the last year, with a mean time of nine hours per week. The mean age was 31 years, indicating that it is not only children and adolescents participating in gaming [1]. Gaming has several positive effects, for example, increased cooperative ability, spatial perception, flexibility in attention and problem solving [2–6]. Gaming has also been used as a tool in health care, for example, to improve balance, increase physical activity through exercise games and in the treatment of post-traumatic stress disorder (PTSD) [7–11]. For most people, gaming is associated with pleasure and recreation and engaging in gaming is also positively correlated with good mental health [12, 13]. Moreover, gaming can also be used as a coping mechanism for underlying difficulties. Some individuals find social acceptance in the gaming community, which they may not otherwise experience in their daily lives [14]. Other individuals may appreciate the structure and predictability of the games, for example, in extensive multiplayer online games [15]. However, as the popularity of gaming increases, the negative effects of gaming have been more commonly observed [16].

For some individuals, gaming takes up an increasingly large part of life and eventually affects work, school and personal relationships. When the new version of the World Health Organization´s diagnostic classification system (ICD-11) was presented in 2018, gaming disorder (GD) was included as a diagnosis [17]. Gaming disorder is described as a pattern of persistent or recurrent gaming behavior (digital- or video-gaming), which may be online or offline, and is defined by the following three criteria 1) impaired control over gaming 2) increasing priority given to gaming to the extent that gaming takes precedence over other life interests and daily activities and 3) continuation or escalation of gaming despite the occurrence of negative consequences.

A few years earlier, the Diagnostic and Statistical Manual of Mental Disorders (DSM-5), presented Internet Gaming Disorder (IGD) as a potential disorder that needs to be studied more extensively [18]. It is suggested that five out of the following nine criteria should be present to meet the criteria for the disorder: 1) high pre-occupation with gaming, 2) withdrawal symptoms, 3) increased tolerance to gaming, 4) unsuccessful attempts to stop or reduce gaming, 5) loss of interest in other hobbies or activities, 6) excessive gaming despite negative consequences, 7) deception about gaming activities towards others, 8) use of gaming as escape or relief from a negative mood, and 9) jeopardized or lost relationships, jobs, or educational or career opportunities.

Gaming disorder has been associated with several different psychiatric comorbidities. For example, previous studies have shown correlations with depression and anxiety [16, 19–21], autism [22], and Attention Deficit Hyperactivity Disorder (ADHD) [23]. In addition, many individuals diagnosed with GD experience low quality of life [24].

It is still not fully known why an individual develops GD. It is likely that it can not be explained by one single factor. Király et al. suggests that three different factors could affect the development of GD: gaming related, individual and environmental factors [19]. For example, gaming companies design games to be as engaging and rewarding as possible. Further, individual risk factors may also play a role. Previous findings point to male gender, younger age and psychiatric comorbidity as risk factors for GD. Family, school and individual infrastructure for gaming can be seen as environmental factors affecting gaming habits [19]. In an influential model, Brand et al. [25] summarized research on different kinds of behavioral addictions, including GD, and developed a theoretical model showing how unproblematic behavior can develop into addiction. Specifically, the model describes how predisposing individual vulnerabilities, together with cognitive and affective responses, can cause behaviors to become addictive, and how these interactions change during the addictive process. They describe the early stages of the addictive process as characterized by gratifying experiences when engaging in the behavior, but that the behavior is controlled by active decisions to engage in it or not. In later stages, the behavior is instead more habitual and difficult to control and may also more often serve to avoid negative feelings than being a purely rewarding activity [25].

Gaming disorder can cause both personal suffering, absenteeism from school or job and societal costs, as the individual is unable to function in his or her everyday life. Losing important years in school could have major consequences later in life. Thus, it is urgent to establish an effective treatment for GD since there is currently no “gold standard”. Several methods have been studied, with varied results. One of the most studied approaches is cognitive behavioral therapy (CBT). However, the level of evidence for CBT is still low due to methodological reasons and poorly designed studies, lowering the quality and degree of evidence. In a recent meta-analysis that included 38 studies, it was concluded that CBT seems to have a good effect, but the reliability of the results may have been biased due to the inclusion of small studies with low scientific quality [26].

For GD, no evidence-based CBT program for adolescents and adults exists in Sweden. Therefore, we aim to evaluate a CBT-manual based on standardized modules which can be flexibly combined depending on individual needs.

### Objectives {7}

The primary objective of this trial is to examine the effects of a 12-week CBT-intervention on GD-symptoms, compared to a waitlist control. The secondary objective is to study the effects on weekly hours of gaming. The hypothesis is that CBT will lead to a reduction of GD-symptoms and a decrease of weekly hours in gaming, compared to the wait list control.

### Trial design {8}

The study is designed as a two-armed RCT with an allocation ratio of 1:1 to each arm. The primary endpoint is symptoms of GD at end of treatment (time point 3). We aim to investigate if the group receiving active treatment have better outcomes than the wait list control, hence the study is designed as a superiority trial.

## Methods: participants, interventions and outcomes

### Study setting {9}

This is a single-center study including participants from all geographical areas of Sweden. The trial will be performed at the Clinic for Gambling Disorder and Screen Health, Sahlgrenska University Hospital, Gothenburg, Sweden, and the treatment sessions will be held on site at the clinic or digitally via computer or smartphone. The clinic specializes in the treatment of gambling and gaming disorder.

### Eligibility criteria {10}

There are four criteria for inclusion: 1) meeting at least five out of nine diagnostic criteria for IGD according to the DSM-V; 2) 15 years of age; 3) able to read and write in Swedish; 4) provide informed consent to participate in the study. Exclusion criteria are as follows: 1) somatic or psychiatric disease that is contraindicative for treatment or that seriously limits participation in the study (e.g., ongoing psychotic, manic or hypomanic episode or neurodevelopmental disorders with severe disability); 2) an ongoing significantly elevated risk of suicide (based on assessment in a structured clinical interview); 3) participation in another ongoing psychological treatment with a similar content as in this trial, or plan to start such treatment during the time of the study; and 4) has started or changed medication for any psychiatric problem during the last month.

The intervention will be conducted by clinical psychologists with documented experience in CBT.

### Who will take informed consent? {26a}

Informed consent will be obtained by a research assistant, either digitally or on paper. The digital consent form will be signed using a secure electronic ID (Bank-ID, Finansiell ID-Teknik BID AB).

### Additional consent provisions for collection and use of participant data and biological specimens {26b}

N/a. No biological specimens will be collected in this study; therefore, no additional consent will be obtained.

## Interventions

### Explanation for the choice of comparators {6b}

Today, no evidence based “gold standard” treatment exists for GD. Therefore, there are no obvious choices of comparators. For this reason, the CBT treatment is compared to a waitlist control. Participants in the waitlist control group will, after the control period, be offered the same treatment as participants in the intervention group.

### Intervention description {11a}

Every patient that seeks treatment for GD at the clinic will be booked for an initial clinical interview with a psychologist or social worker. Before the visit, the patients will answer a number of questionnaires (see Table 2, Timeline). Included in the first interview is a semi-structured diagnostic interview about GD; sociodemographic and anamnestic information; current psychiatric status, including assessment of suicidal risk; and gaming habits. Patients meeting the inclusion criteria for the study will receive information about the trial.

After initial assessments, a research assistant will contact all patients by telephone and go through the Mini International Neuropsychiatric Interview (M.I.N.I.−7.0.1) [27]. The M.I.N.I. is a brief interview aimed at detecting psychiatric comorbidity (see Sect. 18a) and will enable further identification of reasons for exclusion. If no exclusion criteria are met, the patients will be asked about participation in the study. Patients that accept will sign the informed consent form.

Before randomization, participants will be invited to a psychosocial assessment conducted by a social worker. Topics covered in the interview will include living situation, financial situation, and social network. If any difficulty is identified and deemed to have a negative effect on the possibility of taking part in the treatment, an intervention will be initiated. For example, an individual with difficulties taking care of the household may need support from social services.

If no other interventions are needed before CBT treatment, the participants will be randomized to one of the two arms: the intervention group or the control group. For participants that need extra interventions before the treatment starts, randomization will be postponed until it is deemed appropriate to start the treatment.

#### Intervention group

##### CBT manual

The main part of the intervention is based on a CBT manual comprising nine different modules, each addressing an area identified as problematic for a majority of this patient group, for example, “Making gaming more difficult” (to address problems associated with diminished control over gaming) and “Emotions” (because gaming often serves as a dominant strategy to regulate emotions) (see Table 1). In addition to the main modules, there will also be three optional modules with content valid for some of the participants. Every participant will have an individual treatment plan, including the main and optional modules corresponding to individual needs and difficulties related to gaming. Based on clinical judgment, the length and number of modules may therefore differ between patients.

**Table 1 Tab1:** Modules included in the CBT manual

Module	Content
1	Goal setting
2	Understanding your gaming
3	Planning of time
4	Making gaming more difficult. Mid-treatment assessment
5	Alternative activities
6	Procrastination
7	Emotions
8	Thoughts
9	Relapse prevention. Post-treatment assessment
Optional	Support for home assignments
Optional	In-game purchases
Optional	Handling obstacles

The sessions are planned for a duration of between 45 to 60 min. During each session, the psychologist will review last week's homework together with the participant and present a new topic. If more time is needed for last week’s topic, this will be accommodated. In between every session the participants will work on take home assignments related to the different topics.

To ensure treatment fidelity over time, the therapists will document which parts of each module have been covered in the session.

The treatment will last for approximately 12 weeks, with one session every week, and will be led by clinical psychologists with good experience in CBT. Assessments will be made at the first, fourth and last session (T1, T2 and T3, see Table 2, Timeline).

**Table 2 Tab2:**
[figure not shown]
Timeline for participants included in the trial

*T* Timepoint, *CBT* Cognitive Behavioral Therapy, *IGDS9-SF* Internet Gaming Disorder Scale-Short Form, *GDT* Gaming Disorder Test, *GD-TLFB* Gaming Disorder- Time Line Follow Back, *PHQ-9* Patient Health Questionnaire -9, *GAD-7* General Anxiety Disorder-7, *NODS-PERC* National Opinion Research Center DSM-IV Screen for Gambling, *DERS-16* Difficulties in Emotion Regulation Scale, *BBQ* Brunnsviken Brief Quality of Life Scale,
*MOGQ-14* Motives for Online Gaming Questionnaire, *AUDIT* Alcohol Use Disorders Identification Test, *DUDIT* Drug Use Disorders Identification Test, *ASRS* Adult ADHD Self-Report Scale, *RAADS* Ritvo Autism and Asberger Diagnostic Scale, *NEQ* Negative Effects Questionnaire

#### Family sessions

Each participant’s family and/or close friends will be offered 3–4 sessions together with the participant and a social worker, in parallel with the CBT treatment. The purpose is to set common goals, provide information on how the family can support the participant through the treatment, and give advice on how to communicate within the family.

#### Control group

Participants allocated to the control group will be put on a waitlist for approximately 12 weeks. The participants in the control group will be distributed the same questionnaires and gaming diary at the same time points as the intervention group (see Table 2, Timeline). After the waitlist period, the participants in this group will be offered the same treatment as the intervention group.

### Criteria for discontinuing or modifying allocated interventions {11b}

Some factors may lead to the discontinuation or modification of the intervention: 1) the participant wishes to withdraw from the trial, 2) the occurrence of some of the exclusion criteria, 3) incidence of serious adverse events (e.g. hospitalization, suicide attempt or significant worsening of psychiatric symptoms requiring extensive additional out-patient care). and 4) other problems are judged to be more severe than GD and more important to address (e.g. if a personal crisis occur or if it due to problems in school is judged to be more important to focus all efforts on school interventions).

### Strategies to improve adherence to interventions {11c}

Several steps have been taken to increase the participant´s ability to follow the protocol. The participants will receive a reminder by SMS before each session. At every session, the participants will also be reminded of the importance of doing the home assignments and filling out the gaming diary. Besides being an important part of the treatment, the gaming diary is also a method for monitoring adherence to the protocol. Research personnel will monitor whether the questionnaires are answered as planned and provide reminders to the therapists or participants. If needed, the participant will be encouraged to involve family or close friends in the treatment, to help with home assignments or other practical engagements. Also, the amount of time allocated to the different modules will be adjusted based on individual needs. The length and order of each module will be carefully documented in the medical journal. The participants will also be urged to contact the clinic if any problem occurs during the treatment period.

### Relevant concomitant care permitted or prohibited during the trial {11d}

Any treatment of somatic illness will be permitted during the study. However, psychological, or psychiatric treatment with a similar content as in this trial will be prohibited. Starting or changing medication for any psychiatric problem during the treatment period will be registered but not prohibited.

### Provisions for post-trial care {30}

If a participant needs extra support or care after the CBT treatment it will be provided at the clinic or the participant will be referred to the appropriate treatment provider. During the telephone follow-up (3 months after end of treatment) it will be possible to identify patients that may have a relapse in GD and provide further care. After the active treatment period, the participants will be free to seek any form of care they need.

All participants will be covered by a patient insurance and will be able to seek compensation if they have suffered harm from treatment.

### Outcomes {12}

#### Primary

The primary outcome of this study is symptoms of GD. To measure symptoms of GD, a Swedish version of the Internet Gaming Disorder Scale 9—Short Form (IGDS9-SF) will be used. This is one of the most frequently used questionnaires internationally for measuring symptoms related to excessive gaming [28]. It is based on the nine criteria for IGD in the DSM-5. The primary endpoint will be the mean change in IGDS9-SF from baseline to end of treatment and will be distributed at all time points for data collection (see Table 2, Timeline).

#### Secondary

Weekly hours of gaming will be monitored during the treatment and control period, using the Gaming Disorder Timeline Follow-Back (GD-TLFB). The mean change from the start of treatment to end of treatment will constitute the outcome for GD-TLFB. Gaming time is not directly connected to GD [29], but spending excessive amounts of time gaming has been identified as a risk factor for GD [30].

To complement the diagnostic criteria in the DSM-5, a shorter questionnaire based on ICD-11, the Gaming Disorder Test (GDT), is included in the test battery, [31, 32]. The mean change from baseline to end of treatment will constitute the outcome for GDT, that will be distributed at all time points for data collection (see Table 2, Timeline).

#### Exploratory

The occurrence of, and possible effect of the intervention on comorbidity of depression and anxiety will be used as exploratory outcomes of this trial. These conditions will be assessed using the Patient Health Questionnaire-9 (PHQ-9) [33] and General Anxiety Disorder 7-Item Scale (GAD-7) [34]. Previous research has shown that both depression and anxiety are common in patients with GD [16, 19–21]. Data for depression and anxiety will be collected at every time point for assessment (see Table 2, timeline), and data will be aggregated as the mean change from baseline to follow-up.

We will also screen the participants for gambling problems using the National Opinion Research Center DSM-IV Screen for Gambling (NODS-PERC) at time points 0, 3 and 4. Emotional regulation will be assessed by the Difficulties in Emotion Regulation Scale (DERS-16) at time points 0, 3 and 4.

Another area of interest is quality of life. Data from our pilot study showed low levels of quality of life among patients with GD [24]. In order to determine the treatment's effect on quality of life, the Brunnsviken Brief Quality of Life Scale (BBQ) [35] will be used. This questionnaire will be included in the data collection at time points 0, 3 and 4. Mean change from baseline to follow up will be used as outcomes for the BBQ. In addition to questionnaires concerning psychological health, the participants will also answer several gaming related questions, for example, main type of game or if the participant plays alone or with others.

It has also been seen that individuals with GD seem to have a low level of physical activity [36], which is a risk factor for poor physical and psychological health [37, 38]. We want to study the level of physical activity at baseline and investigate whether a decrease in gaming time increases the time spent engaged in physical activity. At time points 0, 3 and 4, the participants will answer questions regarding physical activity level and sedentary time.

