#### Brunnsviken Brief Quality of Life Scale (BBQ)

The Brunnsviken Brief Quality of Life Scale was developed in Sweden to measure an individual´s subjective quality of life in a clinical setting [35]. The questionnaire is divided into six different life areas such as “view on life”, “creativity” and “friends and friendship”. Each life area is represented by two statements: the first applies to “satisfaction” and the second applies to “importance”. Both statements are answered on a five-step Likert scale, scored visually from 0–4, with 0 representing “do not agree at all” and 4 “agree completely”. The score on the “satisfaction” statement is multiplied with the “importance” statement. Thus, the total possible score is 96, with higher scores indicating higher perceived quality of life, and with a suggested clinical cut-off score at 52.5. The Cronbach´s alpha was 0.76, and the internal validity was shown to be 0.82. The BBQ will be included in the initial measurements (T0), post-treatment (T3) and at the 3-month follow-up (T4).

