## Statistical methods

### Statistical methods for primary and secondary outcomes {20a}

Descriptive data will be presented by treatment arm and, where applicable, by timepoint. For numeric variables, summary statistics will include the number of available and missing measurements, mean, standard deviation (SD), median and minimum and maximum values. Treatment comparisons for primary, secondary and exploratory endpoints will be conducted using analysis of covariance (ANCOVA), adjusted for baseline values.

The primary efficacy analysis, which assesses the change in IGDS9-SF from baseline to 12 weeks between the CBT and control groups, will be conducted using analysis of covariance, adjusted for baseline values, with missing data handled through multiple imputation using predictive mean matching. The treatment effect will be tested at a significance level of α = 0.05. Results will be reported as the mean difference with 95% confidence intervals.

Secondary efficacy analyses of changes in GDT and GD-TLFB from baseline to 12 weeks between the CBT and control groups will be conducted using the same methodology as the primary efficacy analysis. To control the overall Type I error rate for secondary endpoints, an alpha-splitting testing procedure will be employed. The two secondary endpoints—GD-TLFB weekly hours and changes in GDT scores from baseline to 12 weeks—will initially be tested with an alpha level of 0.025 each. If the first test (i.e., GD-TLFB) demonstrates statistical significance, the entire probability mass will be transferred to the next secondary endpoint (i.e., GDT), which will subsequently be tested at the 0.05 significance level, with results reported as the mean difference and corresponding 95% confidence intervals.

All statistical tests will be two-tailed, with results presented as mean differences and accompanied with corresponding 95% confidence intervals.

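### PHQ-9, GAD-7 and BBQ outcomes are set at follow-up, after the waitlist has been offered CBT, so the arm comparison becomes early versus delayed CBT

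*Protocol article*

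**What the plan says.** The Outcomes {12} section of the protocol article uses two different end points in time.

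- **Primary:** "The primary endpoint will be the mean change in IGDS9-SF from baseline to end of treatment".
- **Secondary:** "The mean change from baseline to end of treatment will constitute the outcome for GDT". The gaming diary (GD-TLFB) also runs to the end of treatment.
- **Exploratory, PHQ-9 and GAD-7:** "data will be aggregated as the mean change from baseline to follow-up".
- **Exploratory, BBQ:** "Mean change from baseline to follow up will be used as outcomes for the BBQ". The stated purpose is "In order to determine the treatment's effect on quality of life".

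Statistical methods {20a} then says: "Treatment comparisons for primary, secondary and exploratory endpoints will be conducted using analysis of covariance (ANCOVA), adjusted for baseline values". It gives 12 weeks as the time for the primary and secondary analyses, and no time for the exploratory ones.

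On the waitlist arm, the Control group section says: "After the waitlist period, the participants in this group will be offered the same treatment as the intervention group". The waitlist lasts about 12 weeks.

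**The concern.** The trial asks what CBT does compared with no treatment. That question can be answered only while the control arm is untreated, which means up to T3. If the exploratory outcomes are compared between arms at T4, both arms have by then had, or been offered, the same programme. The estimate answers a different question, and it shrinks if the treatment works and its benefit lasts.

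The risk is one of interpretation. A small or null T4 difference in depression, anxiety or quality of life could be read as CBT having no effect on them, when the likely cause is that the controls were treated too.

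**Working it through.** **Step 1. What follow-up means.** The exploratory sentences do not name a time point, so the meaning has to come from the rest of the article.

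- The IGDS9-SF description attaches follow-up to T4, at three months.
- The BBQ description separates the two occasions ("post-treatment (T3) and at the 3-month follow-up (T4"). The AUDIT and DUDIT descriptions make the same separation.
- Plans for assessment {18a} places the follow-up contact three months after treatment ends.
- Within Outcomes {12}, the primary and secondary outcomes use end of treatment, while PHQ-9, GAD-7 and BBQ use follow-up.

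T4 is therefore the natural reading, by strong inference.

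**Step 2. What the control arm has received by T4.** Inputs are a waitlist of about 12 weeks (Control group), CBT of about 12 weeks (CBT manual), and follow-up three months, or about 13 weeks, after treatment. If controls start CBT directly after the waitlist, they finish at about week 12 + 12 = 24.

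- If control T4 is matched to the intervention arm, it falls at about week 12 + 13 = 25, when controls are at or near the end of their own CBT.
- If control T4 is counted from their own treatment, it falls at about week 24 + 13 = 37, when they have completed it.

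On neither timing is there an arm kept untreated by design.

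**Step 3. Reproduce the plan's own figure.** Sample size {14} gives a difference of 5, SD 10, two-sided alpha 0.05 and power 80%. The standardised effect is d = 5/10 = 0.5. The two-sample t-test needs 63.77, so 64 per arm and 128 in total; power at 64 per arm is 0.801. With 20% drop-out, 128/0.8 = 160. The stated figures reproduce. The article states no effect size or power for PHQ-9, GAD-7 or BBQ.

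**Step 4. Illustrate the dilution.** Let u be the share of controls who have had equally effective CBT by T4, and r the share of its T3 gain that the intervention arm keeps. With the SD held constant,

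d(T4) = 0.5 × (r − u).

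With r = 1 and 64 per arm (t-test, two-sided alpha 0.05):

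| Uptake u | d at T4 | Power |
|---|---|---|
| 0% (same as T3) | 0.50 | 80% |
| 25% | 0.375 | 56% |
| 50% | 0.25 | 29% |
| 70% | 0.15 | 13% |
| 80% | 0.10 | 9% |
| 90% | 0.05 | 6% |
| 100% | 0 | 5% (alpha) |

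If the intervention arm keeps 80% of its gain (r = 0.8), the contrast is 0.5 × (0.8 − 0.8) = 0 at 80% uptake, and 0.5 × (0.8 − 1) = −0.10 at full uptake, a slight reversal. The values of u and r, and the use of d = 0.5 for these scales, are assumptions and do not come from the article.

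**The case against.** The best defence is that the article never writes down a T4 test between arms. The exploratory sentences describe how scores are summarised, and the ANCOVA sentence gives exploratory endpoints no time. The word follow-up is not used with full consistency: the retention section {18b} calls T4 a post-treatment assessment and speaks of follow-ups in the plural. The timeline table is not shown. The time point could also be settled in an analysis plan that is not at hand. Finally, these outcomes are exploratory and lie outside the alpha-splitting procedure.

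Part of this stands. T4 is an inference, and the consequence is limited to exploratory outcomes. But the point does not rest on missing detail. The article does state an outcome time, it differs from the one used for the primary and secondary outcomes, and no other time is given for the between-arm analysis. If T3 was meant, the text contradicts the intention and needs the same edit.

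A reader might infer three stronger things, none of which the article supports.

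- **That a real effect is cancelled at T4.** This needs full uptake and equal, lasting benefit. CBT is only offered to the waitlist arm, so dilution is the general result.
- **That the trial will report no effect on these outcomes.** All three scales are also measured at T3, results are to be described by arm and, where applicable, by time point, and nothing prevents a T3 comparison.
- **That no randomised comparison exists at T4.** Early versus delayed CBT by allocated arm is still randomised. It answers another question.

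**Conclusion.** The point holds in a limited form. As written, the between-arm outcome for PHQ-9, GAD-7 and BBQ is most naturally read as change to T4. At that time the trial compares early with delayed CBT and cannot estimate CBT against no treatment. If CBT works and lasts, the direction of the distortion, toward zero, follows from the design.

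Its size depends on assumptions. On the illustrative inputs, 80% power at T3 becomes between 29% and 5% at T4 as uptake goes from 50% to 100%. The real loss depends on the true effect on these scales, the uptake among controls, and durability, none of which the article gives. The primary and secondary conclusions at T3 stand.

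**What to change.** In the Exploratory part of Outcomes {12}, define the between-arm comparison for PHQ-9, GAD-7 and BBQ as change from baseline to T3 (12 weeks), in line with the primary endpoint. Do the same for the other exploratory scales measured at T3. State this time for exploratory endpoints in Statistical methods {20a} as well.

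Report T4 within arm as a description of how results are maintained. If an arm comparison at T4 is kept, label it as early versus delayed CBT and say that it does not estimate the effect of CBT against no treatment.

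The cost is a few words per outcome. No data collection changes, because all three scales are already scheduled at T3, and the T4 data are still used. The edit should be made before outcome data are analysed, and any separate analysis plan should be brought into line with it.
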